### Protection of risks

To reduce any risks associated with tDCS/tRNS, participants will be closely monitored throughout the stimulation sessions and encouraged to report any discomfort. Should they experience uncomfortable scalp sensations or headaches, the stimulation will be immediately halted. All tDCS/tRNS sessions will be conducted and supervised continuously by a trained experimenter.

### Sample size

The sample size is calculated on the primary outcome by *a priori* analysis in G*Power, version 3.1.9.7 (The G*Power Team, Düsseldorf, Germany). Based on the study design and assumptions, the estimated results suggest that participants who receive a single session of active tDCS or hf-tRNS will demonstrate an improvement in TEXT reading accuracy compared to their baseline performance. On the other hand, participants who receive a single session of sham tDCS or sham tRNS are not expected to show a significant change in their performance compared to baseline. While the design of this project has never been employed in DD, we will refer to (i) a previous study by Costanzo and collaborators (16) who prove the effectiveness of a one-session active left anodal/right cathodal tDCS over temporo-parietal regions in a within-subject design; (ii) a study with similar features (e.g., one-session, sham-controlled experiment, comparing baseline vs. tDCS vs. tRNS vs. sham) assessing other cognitive functions (35).

Based on these previous results, to be cautious and conservative, we estimate a medium effect size (f) of 0.25. With an estimated *f* = 0.25, α value = 0.05 (i.e., probability of false positives of 5%), and *β* = 0.80 (i.e., at least 80% power), the sample size is 24 as calculated using a Repeated Measures-Analysis of Variance (RM-ANOVA) model with four within factors (i.e., baseline, active tDCS, active hf-tRNS, and sham).

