Concerning reading speed, syllables per seconds (syll/s) will be considered by dividing the total number of pronounced syllables by the time taken to complete the reading task (in seconds) for all tasks (TEXT, HF, LF, NW).

To ensure that the six versions of each reading task (TEXT, HF, LF, and NW) are comparable in terms of difficulty for both accuracy and speed, a pilot study was conducted with a group of typically developing readers. This preliminary investigation helped determine that the task versions will be appropriately matched in difficulty across the different conditions (see Supplementary materials S3).

The primary outcome of the study will be the changes in TEXT reading accuracy during the active tDCS and active hf-tRNS sessions compared to the sham session (tDCS/tRNS), in comparison to the baseline measurement on Day 0. The primary outcome has been defined based on the results of Costanzo et al. (16), whereby a single session of active left anodal/right cathodal tDCS over temporo-parietal regions led to significant improvements on TEXT reading accuracy compared to control conditions.

Similarly, the secondary outcomes of the study will examine changes in TEXT reading speed, as well as changes in the accuracy and speed of the other reading tasks (HF, LF, and NW) during the active tDCS and active hf-tRNS sessions compared to the sham session (tDCS/tRNS), in comparison to the baseline measurement on Day 0.

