### Statistical analyses and expected results

The Shapiro–Wilk test will be used to test the normality of the data and Levene’s test for the homogeneity of variances. When data will be normally distributed and the assumption of homogeneity will not be violated, parametric analyses will be computed. When one assumption will not be met, non-parametric tests will be conducted or a log-transformation of the distribution will be applied. Sphericity will be verified by Mauchly’s sphericity test and when not met, Greenhouse–Geisser correction will be applied.

Chi-Square analyses will be used to compare the groups on demographic and safety and blinding measures (categorical variables).

Covarying for age, a preliminary analysis to test the effect of the four repetitions (Day 0, Day 1, Day 2, and Day 3) of the reading tasks (accuracy and speed of TEXT, HF, LF, and NW) will be conducted.

RM-ANOVA will be used to compare reading measures (TEXT, HF, LF, and NW accuracy and speed), separately, with conditions (Day 0, A, B, C) as a within-subjects factor and age as covariate.

*Post hoc* comparisons will be assessed using Tukey’s honest significance test.

Partial eta squares (η_p_^2^) will be used as measures of effect sizes.

We hypothesize that:

hf-tRNS will be at least as effective as tDCS in improving TEXT reading accuracy compared with sham condition (primary outcome);hf-tRNS and tDCS will improve performance in the remaining reading tasks (TEXT reading speed and HF, LF, and NW reading accuracy and speed) compared with sham condition;hf-tRNS and tDCS will be as safe as sham condition (i.e., neither tDCS nor hf-tRNS will induce severe AEs or lead to dropouts due to intolerance to stimulation);the blinding will be kept across the conditions.

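### The 80% power claimed for N = 24 belongs to the four-level omnibus F test; each active-versus-sham comparison has about 43% power with Tukey's test at the correlation that reproduces 24

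*Protocol article*

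**What the plan says.** The Sample size section says the calculation was made on the primary outcome, using an a priori "analysis in G*Power, version 3.1.9.7". Its inputs are "we estimate a medium effect size (f) of 0.25" and an alpha of 0.05. The power and the result are tied to a model: "at least 80% power), the sample size is 24 as calculated using a Repeated Measures-Analysis of Variance (RM-ANOVA) model with four within factors", followed by a list of baseline, active tDCS, active hf-tRNS and sham. The same section expects improvement over baseline under either active technique and no significant change under sham. The Conclusion expects the two techniques to have comparable effects.

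The Reading tasks section defines the target. The sentence that opens "The primary outcome of the study will be the changes in TEXT reading accuracy during the active tDCS and active hf-tRNS sessions compared to" goes on to name sham as the comparator, with change taken from Day 0. The first hypothesis under Statistical analyses and expected results is also framed against sham, and adds that hf-tRNS should do at least as well as tDCS.

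That section plans a repeated-measures ANOVA over Day 0, A, B and C with age as covariate. After it, *post hoc* "comparisons will be assessed using Tukey’s honest significance test". No power is given for any active-versus-sham comparison.

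**The concern.** A significant four-level F says only that the four means are not all equal. It can arise from active-versus-baseline differences and does not by itself show that either technique beats sham. The primary question is answered at the pairwise step, and the article attaches its power to the step before.

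A reader who sees a sample size calculated on the primary outcome with 80% power will take that figure to apply to tDCS versus sham and hf-tRNS versus sham. If the real power there is much lower, a non-significant comparison carries far less information than the article suggests. The introduction says the results would inform the development of multi-session hf-tRNS protocols, so this affects what is done next.

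**Working it through.** **Inputs.** From the Sample size section: f = 0.25, alpha = 0.05, N = 24, m = 4 levels. Not stated: the correlation between repeated measures (rho) and the nonsphericity value (epsilon). I assume rho = 0.5 and epsilon = 1 because they return the printed N; a range follows. The pattern of means is the plan's: sham = baseline and both active conditions improved by the same amount d, that is (0, d, d, 0). The age covariate is not modelled. No dropout is assumed, since withdrawn children are replaced.

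**Step 1: reproduce 24.**
- lambda = f² × N × m / (1 − rho) = 0.0625 × 24 × 4 / 0.5 = 12, with df 3 and 23 × 3 = 69. Power is 81.7%.
- At N = 23, lambda = 11.5 and power is 79.7%. The minimum is 24, so the stated figure is correct for the omnibus.
- With rho = 0.4 the same calculation gives 28, and with rho = 0.6 it gives 19. Within the within-factor formula, the printed 24 therefore points to 0.5.

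**Step 2: translate f into an active-versus-sham difference.**
- The means (0, d, d, 0) lie d/2 either side of their grand mean, so f = d/(2 sigma) and d = 2 × 0.25 = 0.5 sigma.
- A paired difference has SD sigma × √(2(1 − rho)) = sigma at rho = 0.5, so dz = 0.5.
- Day 0 is common to all conditions, so it cancels when an active change is compared with the sham change.
- Noncentrality = 0.5 × √24 = 2.449.

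**Step 3: power of each active-versus-sham comparison at N = 24, rho = 0.5.**

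| Test | Critical t | Power | N for 80% |
|---|---|---|---|
| Tukey, four means, error df 69 | 2.633 | 43.3% | 48 |
| Tukey, four means, error df 23 | 2.767 | 39.5% | 50 |
| Paired t, alpha 0.025 (Bonferroni for two) | 2.398 | 53.0% | 41 |
| Paired t, unadjusted | 2.069 | 65.0% | 34 |

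The first critical value is q(0.95; 4, 69)/√2.

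**Step 4: joint results by simulation, same assumptions.** With Tukey, both comparisons are significant in 27% of trials and at least one in 59%. The omnibus is significant while tDCS versus sham is not in 39%. Two paired contrasts with Holm adjustment give about 59% each, 70% for at least one and 48% for both.

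**Step 5: range over rho, with N = 24 and f = 0.25 held.**

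| rho | Omnibus | Tukey, each active vs sham | Unadjusted paired t | N the omnibus calculation would return |
|---|---|---|---|---|
| 0.3 | 66% | 29% | 51% | 32 |
| 0.5 | 82% | 43% | 65% | 24 |
| 0.6 | 90% | 54% | 75% | 19 |
| 0.7 | 97% | 70% | 86% | 15 |
| 0.8 | 99.7% | 89% | 96% | 11 |

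**The case against.** The strongest reply is that nothing printed is miscalculated. The 24 reproduces, and the article openly names the four-level model it came from. That stands: this is a mismatch between the powered test and the primary question, not an arithmetical error. But the section also says the calculation was made on the primary outcome, and that outcome is each active session against sham.

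A second reply is that repeated reading scores from the same child may correlate more strongly than 0.5. This also stands in part. From rho = 0.6 a Tukey comparison is more likely than not to succeed, so a flat statement that a true effect would probably be missed goes too far. The sponsor cannot use both values, though: at rho = 0.6 or above, the calculation would have given 19 or fewer.

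A third is that f = 0.25 does not fix the pattern of means. With one active condition and sham at the extremes and the other two levels midway, dz is 0.707 and Tukey power for that one pair is 79%. That pattern contradicts the stated expectations of sham equal to baseline and comparable active effects.

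Three stronger readings are tempting and not supported:
- A reader might infer that Tukey's test here rests on a pooled error that fails without sphericity. The article names the test but no error term, and may leave that to a fuller document.
- A reader might call the four Tukey pairs other than active-versus-sham irrelevant. The article has expectations about change from baseline, and tDCS versus hf-tRNS is part of the primary hypothesis.
- A reader might assume that a non-significant pair would be reported as evidence against a technique. No section says so, and the study is described as proof of concept.

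**Conclusion.** The point holds. The claimed power of at least 80% is correct for the omnibus F and does not apply to the primary comparison. At rho = 0.5, epsilon = 1 and the plan's own pattern of means, each active-versus-sham comparison has about 43% power with Tukey's test. The shortfall does not depend on the choice of Tukey, because with no multiplicity adjustment power is still 65%.

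The 43% is conditional on an inferred correlation. It should always be quoted with its range (29% to 89% for rho 0.3 to 0.8) and with the note that only rho = 0.5, among the values tried, returns the stated N.

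Describing one factor with four levels as four factors, and labelling 0.80 as beta, might be read as further errors of substance. The text beside each makes the meaning clear, so they are wording corrections.

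**What to change.** Keep N = 24 and make these changes:

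1. In Sample size, state that about 82% power applies to the four-level omnibus only, and give the assumed rho and epsilon. Add the active-versus-sham power with its range over rho.
2. For TEXT accuracy, replace the omnibus followed by Tukey with two planned contrasts, tDCS minus sham and hf-tRNS minus sham. Give each a paired error term and apply Holm adjustment. At rho = 0.5 power rises from 43% to about 59% per contrast, from 59% to 70% for at least one, and from 27% to 48% for both.
3. Report tDCS minus hf-tRNS as an estimate with a confidence interval, since the primary hypothesis includes it.
4. Correct the wording to one within-subject factor with four levels, and to power = 0.80.

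The gain is moderate and does not restore 80%. For each active-versus-sham comparison at rho = 0.5, that would take 41 children with the two-comparison Bonferroni paired test or 48 with Tukey. The cost is a less favourable stated power and a protocol amendment. Enrolment began in August 2023, and the section on study conclusion requires a favourable ethics committee opinion before any modification. No additional children are needed.

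### The 80% power stated for N=24 belongs to a four-level omnibus test that includes Day 0; for the primary contrast of each active condition against sham it is about 43% by the planned Tukey test (65% unadjusted)

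*Protocol article*

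**What the plan says.** The Sample size section of the protocol article ties the number to the primary endpoint: "The sample size is calculated on the primary outcome by" an a priori G*Power calculation. Its inputs are an effect size ("we estimate a medium effect size (f) of 0.25"), a significance level ("α value = 0.05 (i.e., probability of false positives of 5"%) and a target ("i.e., at least 80% power"). The result is stated as "the sample size is 24 as calculated using a Repeated Measures-Analysis of Variance (RM-ANOVA) model with four within factors", the four being baseline, active tDCS, active hf-tRNS and sham. In G*Power terms this is one within-subject factor with four levels. The same section expects improvement on baseline under both active techniques and no significant change under sham.

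The Reading tasks section defines the primary outcome as "changes in TEXT reading accuracy during the active tDCS and active hf-tRNS sessions compared to the sham session (tDCS/tRNS"), taken relative to Day 0. The section Statistical analyses and expected results frames the primary hypothesis against sham. It plans a repeated-measures ANOVA over Day 0 and the three conditions with age as covariate, and adds that post hoc "comparisons will be assessed using Tukey’s honest significance test". No power is given for any active-versus-sham comparison.

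**The concern.** The omnibus F test asks whether any of four means differ. It can be significant because the active sessions differ from Day 0, even if neither is shown to differ from sham. Day 0 is not a randomised condition, so a difference from it may also reflect practice or familiarity. The primary outcome asks the narrower question of active against sham. Power for the broad question does not carry over to the narrow one, yet the Sample size section presents it as power on the primary outcome.

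The article says the results should inform multi-session hf-tRNS protocols. A reader who believes the active-sham comparison had at least 80% power could give a non-significant result far more weight against a technique than the trial can support.

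**Working it through.** **Inputs.** From the Sample size section: f = 0.25, alpha = 0.05, power 0.80, m = 4 levels, N = 24. Not stated: the correlation between repeated measures (rho) and the sphericity parameter. I take rho = 0.5 and epsilon = 1, and check them against the stated N.

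**Step 1: reproduce N.** Noncentral F with lambda = N·m·f²/(1 − rho) and df = (m − 1), (N − 1)(m − 1).
- N = 24: lambda = 24 × 4 × 0.0625 / 0.5 = 12, df 3 and 69, power 0.817.
- N = 23: power 0.797.

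So 24 is the smallest N reaching 80%. Other correlations give other answers: 45 (rho 0), 32 (0.3), 19 (0.6), 15 (0.7), 11 (0.8). Three levels instead of four gives 28. The assumed 0.5 is the only value tried that returns 24.

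**Step 2: turn f into an active-sham difference.** Change from Day 0 in an active session minus change from Day 0 in the sham session is active minus sham, because Day 0 cancels. Take sham equal to Day 0 (my reading of the Sample size section) and equal active effects (the Conclusion expects the techniques to be comparable). In the order Day 0, tDCS, hf-tRNS, sham, the means are 0, d, d, 0. Their SD is d/2, so f = 0.25 gives d = 0.5 SD. At rho = 0.5 the SD of a paired difference is sqrt(2 × (1 − 0.5)) = 1 SD, so the paired standardised difference is 0.5. The noncentrality is 0.5 × sqrt(24) = 2.449.

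**Step 3: power for the primary contrast at N = 24.**

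| Test | Power |
|---|---|
| Four-level omnibus F | 82% |
| One active vs sham, Tukey over four levels (critical t = q(0.95; 4, 69)/sqrt 2 = 2.633) | 43% |
| One active vs sham, unadjusted paired t (df 23) | 65% |
| At least one active vs sham, Tukey (simulation) | 59% |
| Both actives vs sham, Tukey (simulation) | 27% |

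In about 23% of simulated trials the omnibus F is significant but neither active condition exceeds sham by Tukey. Allowing for the age covariate (error df 66) leaves the 43% unchanged.

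**Step 4: sensitivity to the unstated inputs.**

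*Correlation.* Under 0, d, d, 0 the squared pairwise noncentrality is half of lambda (6 against 12). An omnibus power of about 82% at N = 24 therefore implies about 43% by Tukey, whatever the correlation. If f and N are held and rho moves instead, both figures move. Tukey power is 29% (rho 0.3), 54% (0.6), 70% (0.7) or 89% (0.8), but those correlations do not give N = 24.

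*Mean pattern, same f, rho = 0.5.*

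| Day 0, one active, other active, sham | Tukey power vs sham |
|---|---|
| 0, d, d, 0 | 43% each |
| 0, d, d/2, 0 | 63% stronger, 13% weaker |
| 0, d, 0, 0 (one technique works) | 58% for that technique |
| 0, d, d, 0.3d (some gain under sham) | 26% each |

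The most favourable arrangement for a single contrast puts sham lowest, one active highest and the other two midway. The difference is then 0.25 × sqrt 8 = 0.707 SD and Tukey power is 79%. That arrangement needs sham to fall below Day 0, which the article does not expect.

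**Step 5: what 24 children can detect.** 80% power for one comparison needs a paired standardised difference of about 0.72 by Tukey (0.711, rounded up) or 0.60 unadjusted. At 0.5, 80% would take 48 children (Tukey) or 34 (unadjusted).

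**The case against.** The strongest reply is that the sizing matches the declared main model. The analysis section plans a four-level repeated-measures ANOVA including Day 0, and N = 24 is correct for it. That stands: a reader might infer that 24 is an arithmetic error, and it is not.

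A second reply is that Day 0 is part of the primary outcome as written. A reader might infer that Day 0 has no place in the endpoint, and the definition does not support that. But Day 0 cancels once active change is compared with sham change, so the contrast to be powered is still active against sham.

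Third, 43% is not the plan's own number. The article gives neither a correlation nor means, and expecting no significant change under sham is weaker than assuming equality with Day 0. This stands, so the figure needs its assumptions and range beside it.

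Fourth, Tukey over all six pairs is strict and labelled post hoc. It is the procedure the plan names, and under the equal-effects pattern the unadjusted figure is still 65%. With unequal effects (0, d, d/2, 0) the stronger technique would reach 81% unadjusted, while the weaker would have 29%.

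Fifth, this is a proof-of-concept study. That can justify 24 children, but not a statement of at least 80% power on the primary outcome.

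**Conclusion.** The point holds as a mismatch between the powered test and the primary contrast. N = 24 gives 82% power for the four-level omnibus F. With sham equal to Day 0 and equal active effects, it gives 43% per active-versus-sham comparison by Tukey, 65% unadjusted, 59% for at least one technique and 27% for both. The other mean patterns tried at the same f run from 13% to 63% per comparison by Tukey, all below 80%. These figures rest on a correlation of 0.5 and sphericity, which reproduce the stated N but are not printed.

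A reader might go further and infer that a true effect of the planned size would more often than not leave the trial with nothing to show against sham. The figures do not support that: it holds for each technique taken singly, but at least one would beat sham in 59% of trials. Nor does the article say that a null result would be read as no effect; the risk is that the stated power invites that reading.

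**What to change.** Keep 24 children and restate the Sample size section, for example:

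*Twenty-four children give 82% power for the four-level omnibus test (f = 0.25, correlation 0.5, sphericity). If sham equals Day 0 and both techniques improve accuracy by 0.5 SD, power against sham is 43% per comparison with Tukey's test (65% unadjusted) and 59% for at least one technique with Tukey's test. Other mean patterns examined at the same f give 13% to 63% per comparison with Tukey's test. Power of 80% for one comparison needs a paired standardised difference of about 0.72 (Tukey) or 0.60 (unadjusted). A non-significant active-sham result will be reported with its confidence interval and not read as absence of effect.*

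If the authors' G*Power run used a different correlation or had other means in mind, they should print those and recompute. The change is to wording only: no extra children, sessions or analyses. The cost is that the stated power becomes less favourable.

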### Statistical analyses and expected results

The Shapiro–Wilk test will be used to test the normality of the data and Levene’s test for the homogeneity of variances. When data will be normally distributed and the assumption of homogeneity will not be violated, parametric analyses will be computed. When one assumption will not be met, non-parametric tests will be conducted or a log-transformation of the distribution will be applied. Sphericity will be verified by Mauchly’s sphericity test and when not met, Greenhouse–Geisser correction will be applied.

Chi-Square analyses will be used to compare the groups on demographic and safety and blinding measures (categorical variables).

Covarying for age, a preliminary analysis to test the effect of the four repetitions (Day 0, Day 1, Day 2, and Day 3) of the reading tasks (accuracy and speed of TEXT, HF, LF, and NW) will be conducted.

RM-ANOVA will be used to compare reading measures (TEXT, HF, LF, and NW accuracy and speed), separately, with conditions (Day 0, A, B, C) as a within-subjects factor and age as covariate.

*Post hoc* comparisons will be assessed using Tukey’s honest significance test.

Partial eta squares (η_p_^2^) will be used as measures of effect sizes.

We hypothesize that:

hf-tRNS will be at least as effective as tDCS in improving TEXT reading accuracy compared with sham condition (primary outcome);hf-tRNS and tDCS will improve performance in the remaining reading tasks (TEXT reading speed and HF, LF, and NW reading accuracy and speed) compared with sham condition;hf-tRNS and tDCS will be as safe as sham condition (i.e., neither tDCS nor hf-tRNS will induce severe AEs or lead to dropouts due to intolerance to stimulation);the blinding will be kept across the conditions.

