### Reading tasks

Four different reading tasks (text – TEXT; high-frequency words – HF; low-frequency words – LF; non-words – NW) will be presented to the participants in the Italian language. Participants will be required to read aloud as quickly and accurately as possible.

TEXT derived from an Italian novel (65). Items in HF list and LF list were matched for Italian written word frequency, number of letters and syllables, bigram frequency (according to CoLFIS)^1^ and mean onset reaction time. To avoid the repetition effect, multiple versions of each reading task will be administered. This will include different versions presented at baseline (before stimulation) and during each stimulation session, resulting in a total of six versions across the study. The purpose of this approach is to minimize the impact of task familiarity. To control for the influence of fatigue, the order of the reading tasks will be counterbalanced between the three conditions (tDCS, hf-tRNS, and sham).

Regarding reading task characteristics, each TEXT will be composed of approximately 400 syllables, each list of HF will be composed of 30 high frequency words (over 70 syllables long), each list of LF will be composed of 30 low frequency words (over 70 syllables long), and each list of NW will be composed of 30 non-words (over 70 syllables long).

For each reading task (TEXT, HF, LF, and NW), both reading speed and accuracy will be measured and considered. Concerning TEXT reading accuracy, an error point will be assigned in presence of substitution, omission, and/or addition of syllables. A 0.5 error will be assigned in case of auto-correction during reading. The number of words correctly read will be considered, and the percentage of accuracy will be calculated via dividing the number of correctly read stimuli by the total number of stimuli presented and multiplying the result by 100. For the remaining tasks (HF, LF, NW), an error point will be assigned in presence of substitution, omission, and/or addition of syllables, while auto-corrections during reading will not be treated as errors. The number of errors will be considered, and the percentage of errors will be calculated via dividing the number of errors by the total number of stimuli presented and multiplying the result by 100.

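### The analysis of TEXT accuracy, the primary outcome, depends on assumption tests, with an unranked choice between a rank test and a log that worsens left skew

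*Protocol article*

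**What the plan says.** Under Statistical analyses and expected results, the protocol article checks normality with Shapiro-Wilk and uses "Levene’s test for the homogeneity of variances". Parametric analysis follows only if both are satisfied. Otherwise: "When one assumption will not be met, non-parametric tests will be conducted or a log-transformation of the distribution will be applied". No rank test is named, the two options are not ordered, and no endpoint is exempt. The same section plans a repeated-measures ANOVA for each reading measure, with Day 0, tDCS, hf-tRNS and sham as the levels of the condition factor and age as covariate. Sphericity is handled separately, by Mauchly's test and the Greenhouse-Geisser correction.

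Under Reading tasks, "The primary outcome of the study will be the changes in TEXT reading accuracy". TEXT accuracy is scored as percent correct. The three list tasks (HF, LF, NW; 30 items each) are scored the other way round: "the percentage of errors will be calculated via dividing the number of errors by the total number of stimuli presented".

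The Sample size section gives 24 participants for a repeated-measures ANOVA with four measurements, alpha 0.05 and 80% power, where "we estimate a medium effect size (f) of 0.25".

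**The concern.** A primary analysis should be identifiable before the data are seen. Here the data decide whether the planned ANOVA is used. If it is not, two quite different analyses are open: a comparison of means on a log scale, or a comparison of ranks.

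The branches also have faults of their own. A log shortens a long right tail, whereas a score with a ceiling at 100 tends to have a long left tail. The usual rank test for this layout, Friedman, has no place for age. Levene's test compares independent groups and is applied here to repeated readings of the same children. At stake are the stated 5% error rate and the link between the analysis that justified the sample size and the one that is reported.

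**Working it through.** **1. The plan's own figure.** Inputs from Sample size: f = 0.25, alpha 0.05, m = 4 measurements, one group. Assumed, because not stated: correlation 0.5 between repeats and sphericity (ε = 1). Noncentrality is f² × N × m / (1 − ρ) = 0.0625 × 24 × 4 / 0.5 = 12, with 3 and 69 degrees of freedom. Power is 0.817, and 24 is the smallest N reaching 80%. The figure reproduces, but it belongs to the ANOVA and not to either fallback.

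**2. Why the log acts the wrong way.** Take three illustrative scores of 60, 90 and 98%. On the raw scale the lower gap is 30 and the upper gap 8, a ratio of 3.75. On the log scale the gaps are ln(90/60) = 0.405 and ln(98/90) = 0.085, a ratio of 4.76. The lower tail is stretched further.

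**3. How often the switch would operate.** The article gives no mean, SD or shape for TEXT accuracy, so these inputs are assumptions: 24 children, four conditions, no true effect, 200 words per text, normal child effects on the logit scale, session SD 0.25 on that scale, 2,000 runs per row. Shapiro-Wilk is applied to each condition's scores. Age is left out.

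| Mean accuracy | Child SD (logit) | Skew raw → log | Any Shapiro-Wilk failure raw → log |
|---|---|---|---|
| 80% | 0.6 | −0.68 → −1.03 | 67% → 90% |
| 88% | 0.6 | −0.92 → −1.15 | 85% → 93% |
| 92% | 0.6 | −1.04 → −1.20 | 91% → 95% |
| 92% | 0.9 | −1.36 → −1.62 | 98% → 99% |
| 95% | 0.8 | −1.40 → −1.55 | 98% → 99% |

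The log made the skew worse and the normality test fail more often in every row. With exactly normal, equal-variance data, four Shapiro-Wilk tests plus Levene still set off the switch in about 20% of trials.

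**4. Type I error in the same runs.** Used alone, raw ANOVA gave 4.8 to 5.4%, log-ANOVA 4.8 to 5.1% and Friedman 4.9 to 5.8%. Counting a trial as positive if either log-ANOVA or Friedman was significant gave 7.7 to 8.7%. Other runs, with 180 words, session SD 0.3 and means of 90 to 97%, gave 6.9 to 7.6% and 5.8 to 7.1%. Simulation error is about half a percentage point, so about 7 to 8% is a fair summary.

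**5. Levene across repeated conditions.** With equal variances and correlations of 0.5 and 0.8 it rejected in 0.1 to 1.5% of trials rather than the nominal 5%. It has the wrong level, but errs towards not rejecting.

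**6. Lists with no errors (secondary outcomes).** The log of zero percent error does not exist. At assumed error rates of 5% and 10% per item, with independent items, the chance of an error-free 30-item list is 0.95^30 = 0.215 and 0.90^30 = 0.042.

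**The case against.** The strongest reply is that this is a journal article, and that naming the rank test and its follow-up comparisons belongs in an analysis plan not shown. For those details this is fair, and they are not held against the plan. But the article is not silent on the switch itself: it states a rule, and the rule leaves the primary analysis open.

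Four stronger readings are tempting, and the document does not support them.

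- *The log is undefined for many TEXT results because the primary outcome is a change, and changes can be zero or negative.* The analysis section models condition scores with Day 0 as a level. The log of a positive percentage exists.
- *The type I error is inflated.* Each branch alone holds about 5%. The excess arises only if both are run and the favourable one is reported, which the article does not say will happen.
- *The fallback will be the real primary analysis.* That depends on left skew and on testing each condition's scores. Entry on an accuracy or a speed deficit makes a ceiling plausible but does not establish it. In a run that tested active-minus-sham differences instead, Shapiro-Wilk failed in only 10 to 25% of trials per contrast.
- *Levene's test will divert the primary analysis.* With equal variances it rarely would. Frequent rejection (71 to 74%) needed a Day 0 SD half that of the sessions, which nothing in the article suggests.

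It is also true that the log does little harm to the error rate, and that near 95% accuracy it changes the skew only modestly. For the list error percentages, where right skew is more likely, a log could even help, apart from the zeros.

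**Conclusion.** The point holds in this form. The primary analysis depends on assumption tests, and its fallback is an unranked choice between two different methods. One of them, the log, cannot repair left skew on a percent-correct scale. The other, in its usual form, loses the age covariate. Levene's test does not fit the design, though it would seldom matter.

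The wording of the rule needs no simulation to establish. The sizes do: failure of at least one Shapiro-Wilk test in about 70 to 97% of trials rests on the assumed ceiling-type scores, and about 7 to 8% type I error is an upper bound under selective reporting. The stated sample size of 24 is unaffected if the ANOVA is kept. The plan should be corrected, but the defect does not undermine the design.

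**What to change.** Delete the assumption-test switch and Levene's test. Name one primary analysis and one scale for TEXT accuracy before unblinding. One suitable choice is the planned repeated-measures ANOVA with age as covariate, the Greenhouse-Geisser correction and its active-versus-sham contrasts. The scale can be raw percent correct or the empirical logit of each reading, log[(correct + 0.5)/(errors + 0.5)].

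Do not log percent correct. Do not log the list error percentages without a stated way of handling zeros. Use residual plots as description only.

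If a rank or permutation analysis is wanted, specify it in advance as a sensitivity analysis. A permutation test must reproduce the allocation method in the Study design section (minimal sufficient balancing over six orders).

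The cost is a few sentences of wording and slightly more programming, with no extra participants or data.
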